#### Qualitative

For mothers in intervention facilities, we will include both women who reported having and not having a positive experience with their labor and birth care from the quantitative survey. We will assess the acceptability of birth companions by interviewing mothers who had a birth companion in intervention facilities. We will also interview their birth companions, including husbands/partner, other family members, and friends. For providers and unit managers, we will select some staff from intervention facilities where birth companion coverage is high and some from where birth companion coverage was low. We will plan to have up to approximately 16 interviews with mothers and birth companions. We will also have approximately eight FGDs with providers and eight KIIs with unit managers (Table 5).

**Table 5 Tab5:** Summary of sample size table for qualitative data collection

Respondent type	Methodology	Estimated number of quarterly of data collection in each country
**Mothers who had a birth companion** in intervention facilities	IDIs to understand experience of care, and experience and acceptability of birth companions	Up to approximately 16 interviews
**Birth companions** in intervention facilities	IDIs to understand acceptability of birth companions	Up to approximately 16 interviews
**Providers** in intervention facilities	FGDs to understand acceptability of birth companions	Up to approximately eight discussions
**Health facility unit managers** in intervention facilities	KIIs to understand feasibility and acceptability of birth companions	Up to approximately eight interviews

### Outcomes

#### Primary outcome

Proportion of women at study facilities that have a birth companion during labor, birth, and the postnatal period.

#### Secondary outcomes

***Experience of care***

Among those who report having a birth companion, proportion who report that the birth companion was the one of their choice.Mothers’ perception of the birth companion experience.Mothers’ score on Person-Centered Maternity Care scale [26], comparing those that have and do not have a birth companion.

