
Use of a birth companion will be voluntary for participants and non-participants who seek care at study site facilities. There are no retention strategies for women or companions for the intervention. Staff at intervention facilities will be supported to implement the package through on-site monitoring and audit and feedback cycle data reviews.

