### Analysis of primary outcomes

Proportion of mothers whose births included birth companions will be reported and compared between intervention and standard care arms at the end of the intervention using cluster-weighted chi-square test [25, 27]. If the baseline data shows difference between intervention and standard care arms in covariates which may affect the outcome, such covariates will be adjusted for using logistic regression model with cluster-correlated standard error estimates to account for the correlation of outcomes within facility.

The model will include birth companion status at birth as the study outcome, study arm as the primary predictor, and adjustment for covariates that are differentially distributed between the study arms. The primary analysis will be conducted separately for each sub-national region.

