### Analysis of secondary outcomes

#### Quantitative

For the binary secondary quantitative outcomes, we will use similar analytical methods as for the primary outcome. For continuous outcomes, such as facility readiness for change or score on the Person-Centered Maternity Care scale, we will use a cluster-weighted t-test. As in the case of the primary outcome, linear regression models with cluster-correlated standard error estimates will be used to compare the study arms while adjusting for covariates that are differentially distributed between the study arms.

If the proportion of missing data on these covariates is more than 5%, we will use statistical imputation for missing data. Similarly, if the proportion of missing outcome data is small (< 5%), then complete-case analyses will be used. If the amount of missing data for the study outcomes is > 5% or if it is suspected that missingness for the outcome data are not completely at random, based on examination of reasons for missingness, a series of sensitivity analyses for the distribution of missing outcome data will be performed.

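### The maternity-care score is defined by companion status in the outcome list but analysed by arm, and a between-arm test of companion-of-choice would condition on the primary outcome

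*Protocol article*

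**What the plan says.** Under Secondary outcomes, Experience of care, the protocol article lists the mothers' score on the Person-Centered Maternity Care scale, "comparing those that have and do not have a birth companion". The same list contains a second outcome: "Among those who report having a birth companion, proportion who report that the birth companion was the one of their choice".

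Under Analysis of secondary outcomes, Quantitative, the score is named among the continuous outcomes: for facility readiness or "score on the Person-Centered Maternity Care scale, we will use a cluster-weighted t-test". That sentence does not name the groups, but the next one does: by analogy with the primary outcome, linear regression models "will be used to compare the study arms while adjusting for covariates that are differentially distributed between the study arms". For binary outcomes the section states: "For the binary secondary quantitative outcomes, we will use similar analytical methods as for the primary outcome". Under Analysis of primary outcomes, those methods are that proportions are "compared between intervention and standard care arms at the end of the intervention using cluster-weighted chi-square test".

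The variable that forms the groups in both experience-of-care outcomes is the primary outcome, "Proportion of women at study facilities that have a birth companion during labor, birth, and the postnatal period". The section on the intervention package adds: "Use of a birth companion will be voluntary for participants and non-participants".

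**The concern.** Facilities are randomised; companions are not. Whether a woman has a companion is settled after randomisation, by her, her family and the facility, and the package is designed to change it.

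**Score.** The protocol itself supplies a route to confounding. The Background lists negative provider attitudes and constraints of space and privacy among the barriers to companions. Data collection describes the score as covering dignity and respect, communication and autonomy, and supportive care. A facility with better attitudes could plausibly both admit more companions and score higher, even if companions did nothing. The package also orients providers and can improve privacy barriers, which may raise the score of women who have no companion. The with/without contrast then estimates neither the effect of the package nor a clean effect of a companion. The planned covariate adjustment is for imbalance between arms, so it does not address selection between companion groups. With two contrasts on the page, either result could later be presented as the prespecified one.

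**Companion-of-choice.** If arms are tested within women who have a companion, the two denominators differ by construction, because the package is meant to bring more women into one of them. A difference can then arise from who enters the denominator.

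**Working it through.** **Plan's own figures (Sample size, Quantitative).** Per site: 62 × 12 = 744 women; control 3 × 62 = 186; intervention 9 × 62 = 558. These reproduce. Assumed endline coverage is 20% control and 50% intervention. The plan gives no figure for either secondary outcome.

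**Groups under each contrast, per site**

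- With a companion: 0.20 × 186 + 0.50 × 558 = 37 + 279 = 316.
- Without: 0.80 × 186 + 0.50 × 558 = 149 + 279 = 428.
- Share from intervention facilities: 279/316 = 88% with, 279/428 = 65% without.
- By arm: 558 against 186.
- Companion-of-choice among those with a companion: 279 against 37.

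**Score, illustration 1: facility-level confounding, companions have no effect.** Difference = Cov(facility coverage, facility score) / Var(companion) = c × sd_b × √(ICC / [p(1 − p)]).

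- p = 316/744 = 0.425, so p(1 − p) = 0.244.
- Coverage ICC: 0.05 to 0.5, the plan's range.
- Assumed: score ICC 0.1, so sd_b = √0.1 = 0.316 SD; facility-level correlation c between coverage and score, 0 to 0.5.

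| c | ICC 0.05 | ICC 0.2 | ICC 0.5 |
|---|---|---|---|
| 0 | 0 | 0 | 0 |
| 0.25 | 0.04 SD | 0.07 SD | 0.11 SD |
| 0.5 | 0.07 SD | 0.14 SD | 0.23 SD |

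For example, 0.5 × 0.316 × √(0.2/0.244) = 0.14 SD. The result is linear in c and scales with the square root of the score ICC.

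**Score, illustration 2: woman-level selection, companions have no effect.** Assume half the women are better supported, with a companion probability 15 points above their arm's mean, and the other half 15 points below. If the better supported score d higher, the difference is 0.5 × 0.5 × 0.30 × d / 0.244 = 0.307d. For d = 0.2 to 0.5 SD this is 0.06 to 0.15 SD. If the package also raises every woman's score by a, add (0.882 − 0.652) × a = 0.23a. With d and a both 0.2 the total is 0.11 SD; with both 0.5 it is 0.27 SD. Neither equals a, the arm effect, nor zero, the companion effect.

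**Companion-of-choice, illustration.** Assume the package alters no one's report of choice. The 20% who would have a companion anyway report choice at 80%; the additional 30% report it at x.

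- Control: 80%. Intervention: (0.20 × 0.80 + 0.30x)/0.50.
- x = 50%: 0.31/0.50 = 62%, a difference of −18 points.
- x = 90%: 0.43/0.50 = 86%, a difference of +6 points.
- Among all women: control 0.20 × 0.80 = 16%; intervention 31% to 43%, a difference of +15 to +27 points.

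The conditional difference changes sign with x. The all-women difference does not in this range.

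**The case against.** **The arm contrast is already planned.** This is the strongest reply. The analysis section names the score and compares arms, and the article makes no causal claim for the with/without comparison. A reader might infer from the outcome list that randomisation is lost for the score. The documents do not support that: it is lost only if the outcome definition overrides the analysis section. What remains is that the two sections disagree and no text says which governs or whether both are meant. This is a conflict in what is written, not a detail left to a statistical analysis plan.

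**Companion-of-choice is a natural quality indicator.** Among women with a companion it suits an aim of feasibility and acceptability, and no section contradicts its definition. The between-arm test is implied by the general sentence on binary secondary outcomes; it is not stated for this item. Coverage by arm is reported as the primary outcome, so a careful reader could multiply the two proportions. All of this stands, and limits the point to the between-arm test.

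**The magnitudes rest on assumptions.** The documents give no score SD, score ICC, facility-level correlation or choice rates. At c = 0 the facility bias vanishes. A reader might infer that the conditional choice outcome will show harm; the range from −18 to +6 points does not support that.

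**The figure of 37 is per site.** Separate analysis by sub-national region is fixed for the primary analysis only. Over five sites the same assumption gives 5 × 37.2 = 186 control women with a companion. More women would improve precision but would not make the comparison randomised.

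**Conclusion.** The point holds in two parts of unequal weight.

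The main part is the conflict on the score. One section defines the outcome by a voluntary grouping formed after randomisation; another compares arms. Only the second is protected by randomisation. This rests on the text alone. The illustrated bias, about 0.06 to 0.23 SD under most of the assumed inputs and zero if facility coverage and score are unrelated and women do not select, shows what could be at stake; it is not an estimate.

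The lesser part is companion-of-choice. The conditional proportion is a valid description. A between-arm test of it conditions on the primary outcome and, at the planned 20% coverage, rests on about 37 control women per site in three facilities. The direction of any resulting distortion is not established.

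The primary outcome, its by-arm test and the sample size are unaffected.

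**What to change.** 1. Under Experience of care, define the score outcome as intervention versus control among all interviewed women, in line with the analysis section.
2. Keep women with versus without a companion only as a labelled observational association, analysed so that within-facility differences are separated from between-facility ones. Facility fixed effects are one way; other models can do this too.
3. Base the between-arm comparison of choice on a yes/no outcome for every interviewed woman: whether she had a companion who was the one she chose. Report the proportion among women with a companion beside it, descriptively.

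No new data are needed: under Data collection, coverage, choice of companion and experience of care are collected from all eligible women in both arms. The cost is a documented amendment to secondary outcome definitions in a trial that is registered and recruiting, with baseline surveys reported complete in two countries. It should be dated before endline results by arm are seen.

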#### Feasibility

4.Proportion of providers and unit managers who report the physical environment of care supports the presence of birth companion during labor, birth, and the postnatal period.

#### Acceptability

5.Mothers’, birth companions’, providers’, and unit managers’ perception of birth companions.

#### Exploratory outcomes

6.Score on facility readiness to change.7.Facility-level costs for updates to physical environment of care and other implementation costs.

### Recruitment and consent process

#### Recruitment

Data will be collected at baseline and approximately quarterly for approximately one year after the birth companion intervention package implementation is introduced in all study facilities. Qualitative data will be collected approximately quarterly at intervention facilities. The recruitment process by study participant type is detailed in Table 6. The recruitment will be done by study staff who will have secondary and post-secondary training.

**Table 6 Tab6:** Recruitment strategy for study participants

Participant type	Recruitment process
**Mothers**	Quantitative data will be collected from all consenting mothers who give birth in selected/participating facilities during the five data collection periods. Pregnant women coming to the facilities for their ANC visit will be provided with an information sheet so they can learn about the study. Providers will also refer women coming to give birth to the study staff so they can find out more about the study. Investigators will provide information, assess the eligibility of the women, and obtain consent before they give birth. If this is not possible, eligibility and consent will be obtained after birth. A subset of mothers giving birth in intervention facilities will also be asked to participate in the quarterly qualitative assessment prior to discharge. We will use data obtained from that quantitative survey in intervention facilities to select women who did and did not have birth companions, who had different types of birth companions (male/female, partner/non-partner, family member/non-family member) as well as those that were and were not satisfied with the experience of care.
**Birth companions**	Mothers recruited for the quarterly qualitative assessment will be asked if they had a birth companion. If present, investigators will approach the birth companions for recruitment into the study.
**Providers**	Study investigators will work with the facility directors or their designees in intervention facilities to identify providers working in the ANC, labor, and birth wards. Once identified, they will be approached and screened for the quarterly FGDs.
**Unit managers**	Study investigators will work with the facility directors or their designees in intervention facilities to identify unit managers from the ANC, labor, and birth wards. Investigators will approach unit managers and screen them for the quarterly KIIs.

Privacy will be ensured by offering study participation (recruitment) in a space in the facility or outside the facility that allows for audio and visual privacy. We do not expect participation in this study to be associated with any mentioned risks.

#### Consent process

Study staff will have a minimum of secondary and post-secondary training. They will be trained on basic research ethics and the study procedures. The Johns Hopkins School of Public Health (JHSPH) Ethics Field Training Guide will be used during the training.

For all study participants, the information that will be collected by this study team will be kept confidential. The information will not be accessed by anyone except the study team, and it will only be used for this research purpose. No individual identities will be used in any reports or publications resulting from the study. Procedures for consenting study participants are described below.

#### Consenting mothers and birth companions

A data collector will be placed at each facility during the data collection periods. Consent documents will be translated into the local languages. If possible, the data collectors will approach women when they arrive at the facility and screen them to assess their eligibility (if this is not possible, they will be assessed for eligibility after the birth). Informed consent will be obtained after the birth in a private space within the facility. For the qualitative study, women who consent to participate in the study will be asked if they had a birth companion. If present, a similar procedure will be followed for consenting birth companions. In the consent process, potential participants will be informed of why they were chosen, their rights as participants, risks, and benefits. Anyone declining consent will not be included in the study. Surveys and interviews will be administered after consenting the clients. Confidentiality will be kept to the maximum standard during data collection and data handling.

#### Consenting providers and unit managers

Providers and unit managers in ANC, labor and birth wards of intervention facilities will be approached for consent for the duration of the study (approximately 16 months) by study staff. Providers and unit managers will be oriented on the study, informed of why they were chosen, their rights as participants, risks, and benefits. Anyone declining consent will not be included in the study. New providers and unit managers will be consented at the time of data collection. All surveys, interviews and IDIs will be administered after consenting the clients. During the baseline survey, providers will be asked to respond to the facility readiness to change survey. For IDIs and FGDs, they will be approached quarterly after the launch of the intervention. For the quantitative feasibility study, providers in the intervention facilities will be approached during the endline survey. Every effort will be made to protect the confidentiality of participants, but due to practical constraints (e.g., size of facility), it may not be possible to guarantee that supervisors will remain unaware of participation.

### Data collection

#### Quantitative

Pre- and quarterly post-intervention data will be collected from facilities. All women who deliver in the intervention and control facilities during the data collection period and meet the eligibility criteria will be interviewed prior to being discharged. Basic demographic data (age, parity, education, marital status, and socio-economic status) will be collected. Structured questionnaires will be used to assess coverage of birth companion, choice of birth companion (if present) and experience of care. The person-centered maternity score has been validated and is a 30-item scale [26]. It has three sub-scales: (1) dignity and respect, (2) communication and autonomy; and (3) supportive care. Furthermore, we will collect data from providers in all facilitiesto assess the facility readiness to change using a standardized tool. This tool has five context assessment domains: (1) commitment and motivation; (2) ability to implement; (3) internal culture; (4) clinical team functionality; and (5) knowledge and ability to do the intervention. This tool is formulated for health facility staff and leaders. At endline, we will evaluate the feasibility of implementing a birth companion intervention package in intervention facilities. We will also conduct a quantitative analysis at endline to assess the cost associated with implementing the birth companion package.

#### Qualitative

To explore the experience of having a birth companion, we will conduct quarterly interviews with mothers in intervention facilities who meet the inclusion criteria. Acceptability of the birth companion intervention will also be assessed quarterly by conducting IDIs with both women who had a birth companion and their birth companions in intervention facilities. Specific topics to be explored with mothers include: their awareness of the birth companion concept; support/advice they received about having a birth companion; their choice and reason for choosing the birth companion; the type of support their birth companion provided; and their experience of/satisfaction with the care from providers in the presence of birth companion. The following domains will be explored with birth companions including their experience of being a birth companion; how they provided support to mother; their self-reported preparedness to be a birth companion; their perceptions of the orientation materials (e.g., videos, posters, and brochures); and the means used to designate them as a birth companion.

To assess the acceptability as well as feasibility of the birth companion intervention from the supply side, we will conduct FGDs with providers in labor and birth wards and KIIs with unit managers who meet the eligibility criteria. FGDs with providers at intervention facilities will include: their experience of being oriented on the birth companion concept; the materials provided for supporting the birth companion intervention; the physical and managerial level support of the birth companion intervention; and, their experience of and attitudes towards having a birth companion during labor, birth and the postnatal period; perceived changes in their communication and relationship with clients (if any); changes in their workloads; sustainability of having birth companions; and, suggested changes to the model required to offer birth companions. KIIs will be conducted with unit managers in intervention facilities to explore the processes, and where present, challenges of developing birth companion SOP; care provider’s orientation; facility adjustments to facilitate birth companions; integrating birth companions into the care provided; and monitoring the birth companion coverage.

### Statistical analysis and power

The following methods will be used to describe group characteristics or differences: for categorical variables, the number, and percent in each category; for continuous variables, the mean, median, standard deviation, quartiles, and range (minimum, maximum). Adequacy of the randomization will be assessed at baseline by comparing characteristics of participants and facilities in intervention and control arms, including demographics, birth companion coverage, and experience of care.

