**Nasarawa**			
1	312	CEmONC	
2	300	CEmONC	
3	135	BEmONC	
4	109	CEmONC	
5	69	CEmONC	
6	64	BEmONC	
7	45	CEmONC	
8	41	CEmONC	
9	37	BEmONC	
10	37	BEmONC	
11	37	CEmONC	
12	36	BEmONC	

We will use a mixed methods approach to assess impact of the birth companion intervention package and measure the study outcomes with exit interviews, health facility register data extraction, in-depth interviews (IDIs), focus group discussions (FGDs), and key informant interviews (KIIs).

There are five data collection periods. We will first conduct a baseline assessment over the course of approximately four weeks, in facilities meeting the inclusion criteria. Health facilities that decline to participate in the study will be replaced by another facility. Facilities will be randomized after the baseline survey in a 3:1 ratio (i.e., for every three facilities that implement the birth companion intervention, one will serve as a control facility). Randomization is stratified by the number of facility deliveries and by country (Ethiopia) or by county or state within a country (Kenya and Nigeria). Intervention facilities will prepare to introduce the birth companion intervention package over the course of approximately two months to facilitate the presence of birth companions during labor, birth, and the postnatal period. Control facilities will continue to provide the local standard of routine care which may or may not include a birth companion. Facilities will not be replaced or reallocated to study arm post-randomization. This study does not place restrictions on facilities or participants regarding participation in other interventions or research.

We will have three quarterly quantitative and qualitative data collection periods, each lasting for approximately one week. We will conduct an endline quantitative survey, approximately 12 months after birth companion intervention initiation. Mothers, birth companions, health care providers, and unit managers in study facilities will have the option to decline to participate in the study.

At the end of the study, control facilities will be supported to implement the birth companion intervention package by staff from an intervention facility that has a birth companion coverage of approximately 50% or higher (see Fig. 2), assuming that one is available. We will provide limited technical and material support during this period.

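### Adjustment of the endline comparison is triggered by differences among women surveyed before randomisation, not among the women analysed

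*Protocol article*

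**What the plan says.** All references are to the protocol article.

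- **Design and setting:** "Facilities will be randomized after the baseline survey in a 3:1 ratio". Intervention facilities then prepare for about two months. The final survey follows: "We will conduct an endline quantitative survey, approximately 12 months after birth companion intervention initiation".
- **Data collection, Quantitative:** "All women who deliver in the intervention and control facilities during the data collection period and meet the eligibility criteria will be interviewed". Each round takes the women giving birth in that round, and no cohort is followed. Age, parity, education, marital status and socio-economic status are recorded.
- **Statistical analysis and power:** "Adequacy of the randomization will be assessed at baseline by comparing characteristics of participants and facilities in intervention and control arms". The list covers demographics, birth companion coverage and experience of care.
- **Analysis of primary outcomes:** coverage is "compared between intervention and standard care arms at the end of the intervention using cluster-weighted chi-square test". Adjustment is conditional: "If the baseline data shows difference between intervention and standard care arms in covariates which may affect the outcome, such covariates will be adjusted" for, by logistic regression with standard errors that allow for clustering. The following paragraph describes the model as including "adjustment for covariates that are differentially distributed between the study arms", with no round named.
- **Analysis of secondary outcomes:** the same approach is carried over.

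**The concern.** The condition "If the baseline data shows difference between intervention and standard care arms in covariates which may affect the outcome" is a stated rule, not a detail left open. It decides which covariates enter a model fitted to endline women by looking at other women, who delivered before any facility was allocated.

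For facility-level characteristics this is reasonable, because the same facilities appear in both rounds. For woman-level characteristics it is not, because the distribution that can confound the endline comparison is the one among the endline women. It can differ from baseline in two ways:

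- **Chance.** Each site has only three control and nine intervention facilities, and each round draws new women.
- **Recruitment after allocation.** The package is promoted in antenatal care and by community health workers in intervention catchments. The section on consenting mothers also places consent after the birth, when companion status is known. A survey completed before randomisation carries no information on differences that arise this way.

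At stake is a report that declares the randomisation adequate from baseline data while the analysed arms differ on a covariate that the trigger did not select.

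**Working it through.** **1. Which women are in which sample.** Baseline precedes randomisation. Endline is about 12 months after initiation, with about two months of preparation in between. The endline women are therefore recruited roughly 12 months after allocation, or 2 + 12 = 14 if initiation is counted from the end of preparation. That they are almost all different women is an inference from this design; the article does not say it in words.

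**2. The plan's own figures.** 62 × 12 = 744, 62 × 3 = 186 and 62 × 9 = 558, as stated. The article does not say which ICC lies behind 62. With an assumed ICC of 0.10 (inside its range of 0.05 to 0.5) and no allowance for unequal cluster size, the design effect is 1 + 61 × 0.10 = 7.1, and the pooled two-sided test of 20% against 50% has 80.1% power. The point below does not depend on this.

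**3. How well baseline balance predicts endline balance.** Assumptions that are not in the article: a binary covariate with 40% prevalence, 62 women per facility in both rounds, facility effects fully stable over time, and no selection after allocation.

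- Variance of the arm difference = 0.4 × 0.6 × (1 + 61 × ICC) × (1/186 + 1/558).
- Correlation between the baseline and endline differences = 62 × ICC / (1 + 61 × ICC).
- Treating the pair as bivariate normal, with 10 points as an illustrative cut-off, gives the last two columns.

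| Covariate ICC | SD of arm difference | Correlation between rounds | Endline difference over 10 points | Of these, baseline difference under 10 points |
|---|---|---|---|---|
| 0.01 | 5.3 points | 0.39 | 6% | 86% |
| 0.05 | 8.3 points | 0.77 | 23% | 46% |
| 0.10 | 11.1 points | 0.87 | 37% | 29% |

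The baseline survey is an informative but incomplete proxy. Facility effects that drift over time would lower the correlation. The 10-point cut-off is arbitrary: a 9-point baseline gap counts here as no difference, although an analyst might well act on it.

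**4. What a missed imbalance does to the primary result.** Bias in the risk difference is approximately the endline imbalance multiplied by the covariate's effect on having a companion.

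| Endline imbalance | Effect 10 points | Effect 20 points | Effect 30 points |
|---|---|---|---|
| 5 points | 0.5 | 1.0 | 1.5 |
| 10 points | 1.0 | 2.0 | 3.0 |
| 20 points | 2.0 | 4.0 | 6.0 |

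The planned difference is 50% − 20% = 30 points.

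**5. The two adjustment sentences side by side.** The first ties adjustment to the baseline data. The second ties it to covariates distributed differently between arms, at an unstated time. If the second repeats the first, an endline-only imbalance is not adjusted for. If it means the endline women, the section contains two different triggers. Either way the wording has to be settled.

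**The case against.** The strongest reply has four parts.

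- **The baseline check suits its purpose.** Facilities are the randomised unit, and comparing them before allocation is the right test of the randomisation. This stands.
- **A flagged covariate is properly adjusted.** It enters the endline model with the endline women's own values, so any endline imbalance in it is handled. If it turns out to be balanced at endline, including it does no harm to the comparison. This also stands.
- **The second adjustment sentence may already cover endline imbalance**, and the analysis section opens with a general plan to describe group characteristics. This is a possible reading, but the text does not settle it.
- **An endline characteristics table is routine content of a fuller document.** Agreed: its absence from a condensed article would not be a point by itself. The trigger is different, because the article does state it.

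A reader might infer that imbalance in the endline sample is neither examined nor adjusted for at all. The first three replies show that the article does not support that.

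A reader might also infer that self-selection could create a large false effect. Take no true effect and 20% coverage everywhere, and let 5% of control births move, all of them women who would have had a companion anyway. Control then reads (0.20 − 0.05)/0.95 = 15.8% and intervention (0.20 + 0.05/3)/(1 + 0.05/3) = 21.3%, a spurious 5.5 points; at 10% moving it is 11.5 points. The arithmetic is right, but this is a worst case: 5% of births is a quarter of all control women with a companion, and they have the least reason to move. If the movers are instead women who would not have had a companion but get one after moving, then at planned coverage control reads 0.20/0.95 = 21.1% and intervention (0.50 + 0.0167)/1.0167 = 50.8%. The difference is 29.8 points against a true 30. Nothing in the article indicates how many women would move or which, and adjusting for demographics need not remove selection on preference for a companion.

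**Conclusion.** The point holds for woman-level covariates. The stated trigger is evaluated in a sample that is not analysed, and the sentence after it does not clearly agree with it. Followed literally, the rule can leave an endline imbalance unadjusted.

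The consequence is moderate. Across imbalances of 5 to 20 points and covariate effects of 10 to 30 points, the bias is 0.5 to 6 points, small against the planned 30 but more important if the true effect is well below plan. These figures rest on an assumed covariate and assumed effects, since the article gives none. This is a rule worth correcting before the endline data are analysed; it does not invalidate the design.

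**What to change.** **Analysis of primary outcomes.** Replace the baseline-difference trigger with a covariate set fixed in advance and adjusted for whatever imbalance is observed:

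- a short list of woman-level covariates already collected, for example from age, parity, education, marital status and socio-economic status, measured in the endline women;
- companion coverage of each facility in the baseline survey.

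Remove or align the second adjustment sentence so that only one rule remains. Keep the list short, because the analysis is run by sub-national region with 12 facilities each. Apply the same rule to the secondary outcomes that inherit it.

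**Statistical analysis and power.** Limit the baseline comparison to the adequacy of facility randomisation. As the check for differential recruitment, compare by arm the demographics of the endline women and the change in each facility's birth volume from baseline to endline, using register data. State that this may not detect or remove selection on preference for a companion.

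**Cost.** A wording change, one extra table and a slightly larger model with few clusters. The demographics are already collected and register extraction is already among the planned data sources.
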